#### Secondary Outcomes

##### PedsQL Generic Core Scales

Child functioning will be measured by both child self-report and parent proxy-report versions of the Chinese PedsQL Generic Core Scales which are suitable for use in ages 8-12 [30]. It has 4 scales with 23 items measuring child physical (eg, I hurt or ache), emotional (eg, I feel afraid or scared), social (eg, I have trouble getting along with other kids), and school functioning (eg, I miss school because of not feeling well). Each item is rated on a 5-point scale from 0 (never) to 4 (almost always). A higher score indicates better functioning. Its Chinese version has been validated in Hong Kong with good psychometric properties [31].

##### Strength and Difficulties Questionnaire

Both child self-report and parent proxy-report versions of the Chinese Strength and Difficulties Questionnaire (SDQ) will be used to measure children’s psychosocial behavior. The SDQ has 5 subscales, including emotional symptoms (5 items; eg, often unhappy, depressed, or tearful), conduct problems (5 items; eg, often loses temper), hyperactivity/inattention (5 items; eg, restless, overactive, cannot stay still for long), peer relationship problems (5 items; eg, rather solitary, prefers to play alone), and prosocial behavior (5 items; eg, considerate of other people’s feelings). Each subscale has a score, and the first 4 subscales generate a total score of difficulties (20 items) [32]. The parent proxy-report version of SDQ in traditional Chinese has been validated and demonstrated satisfactory reliability and validity [33]. The self-reported version has also been used in younger children (aged 8-13 years) with satisfactory results [34].

##### Game Usage Statistics

The user account system will capture all in-app/task-specific actions taken by the player, including login time, gameplay duration, total game points, the number of correct and incorrect responses in each safety domain (ie, home safety, road safety, and sport-related safety), and the number of attempts needed to reach the correct answer. The account system will only be accessible to the members in the research team, and all user data will be encrypted with a unique password generated by the research team. The usage data will be retrieved from the account system for process evaluation as well as for guiding award reimbursement.

### Data Analysis

Results will be reported from intention-to-treat analysis, where outcome variables of the dropouts will be assumed to be unchanged from the previous assessments to provide a conservative estimate. A complete-case scenario will also be considered as a sensitivity analysis. The effectiveness of the intervention in achieving the proposed targets will be estimated using linear mixed models. Group allocation will be included as dummy independent variable. School will be controlled as random intercepts, whereas covariates, such as child’s age and sex and family socioeconomic status, will be adjusted as fixed independent variables. The linear model will be used for continuous outcomes, whereas logistic and Poisson models will be used for binary and count variables, respectively. The association between total game points and pre–post changes in outcomes will also be analyzed using the linear mixed models among students in the intervention group. Students in the control group will not be considered in this analysis because they will not be able to access the game. Game usage statistics will be added to the model as independent variables.

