### Aims of This Study

This paper describes the protocol for a study that will test the effectiveness of an intervention using a mobile city game, Safe City, to improve the safety knowledge and behaviors of Hong Kong Chinese children in Grades 4-6 by a randomized controlled trial. Our hypotheses are as follows: (1) children in the intervention group (ie, those who receive the Safe City game intervention) will have higher levels of correct safety knowledge and behaviors than children in the control group (ie, those who receive electronic and printed safety information) at 1- and 3-month follow-ups. (2) We expect a change in the children’s functioning and psychosocial difficulties. At 1- and 3-month follow-ups, we expect that children in the Safe City intervention group will show better functions and fewer psychosocial difficulties than those in the control group. (3) We expect that those who play the game more frequently will show greater improvement in safety- and health-related outcomes.

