Figure 1 illustrates the gaming process by which the Safe City game–based intervention may influence the students’ target outcomes. All these game concepts and technical specifications of the game will be stated in the game design document for guiding the development of prototypes of the game. To create an effective and developmentally appropriate learning product, a multiple-phase study approach (collaboration, prototyping, and evaluation) will be employed to produce design prototypes that are developmentally appropriate, comprehensible, and attractive for the end users (children in Grades 4-6) [27]. Collaboration will involve working with game designers and exploring ideas for design prototypes. The prototype game will be played by a group of 4-8 children from the target age group and a debriefing session will be arranged to review their gameplay experiences. The gameplay will be further adjusted based on these end users’ feedback. During the evaluation phase, a 4-week, 2-arm randomized intervention trial will be conducted with 3 data collection periods (baseline and 1- and 3-month follow-ups). Participants will be randomized into 2 groups (the Safe City game intervention group and a traditional health education group) in a 1:1 allocation ratio (Figure 2).

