### Participants

Four districts, including Kwai Tsing, North, Sham Shui Po, and Tai Po, were found to have the highest rates of traffic, domestic, and sport injuries in Hong Kong [5]. All nonspecial, local (noninternational) primary schools in the selected districts will be eligible for participation in the evaluation. Among them, we will recruit 4 schools. Assuming an average of 30 students per class and a participation rate of 70%, the trial will have 4 schools × 3 forms × 4 classes × 30 students × 70% = 1008 participants. Primary schools will be a blocking factor in randomization. All students in Grades 4-6 will be invited to join the trial. Participating students within each school will be randomized with a 1:1 allocation ratio into the intervention or control group. Because the intervention materials will be designed in traditional Chinese, students who are not able to comprehend the Chinese questionnaires at baseline will be excluded from this study. An invitation letter will be sent to all schools in the selected districts. Upon obtaining school consents, informed written consents will be collected from parents of participating students before randomization.

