### Outcomes

#### Primary Outcomes: Safety Knowledge and Behaviors

Child safety knowledge and behaviors will be measured by a questionnaire involving items adopted from the existing literature and questionnaires under the 3 contexts: home safety [28], road safety [23], and sport-related safety [29]. Some item wordings will be modified to ensure their relevance to local environments. Child participants will be asked to indicate their level of involvement in the said behavior (eg, home safety: *use sharps without the presence of my parents*; road safety: *forget to look properly because you are thinking about someone else*; sport-related safety: *play while injured*) on a 5-point Likert scale ranging from “Never” to “Very Often.” They will also be asked to indicate their agreement on safety-related statements (eg, home safety: *never leave food or water unattended on the stove*; road safety: *stop at red lights and stop signs*; sport-related safety: *do warm-up exercise before having any sports activities*) on a 4-point Likert scale ranging from 1=Strongly disagree to 4=Strongly agree. A total score will be generated for each safety context by summing the relevant items. These items will be self-completed by the children at baseline and 1- and 3-month follow-ups. At each follow-up, their parents will also be asked to rate the degree to which children have shown changes in safety knowledge and behavior after the intervention on a 5-point Likert scale ranging from 1=Much worse to 5=Much better.

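### The effectiveness model does not say how a child's three assessments enter it: stacked as written it understates the standard error, and fitted visit by visit it names no baseline adjustment

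*Protocol article*

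**What the plan says.** The Data Analysis section of the protocol article names linear mixed models for the effectiveness comparison and then gives their content: "Group allocation will be included as dummy independent variable. School will be controlled as random intercepts". It adds fixed covariates, introduced as examples rather than as a closed list: age, sex and family socioeconomic status. Dropouts keep their previous value.

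On the primary outcome items, the Outcomes section says: "These items will be self-completed by the children at baseline and 1- and 3-month follow-ups". Hypothesis 1 in Aims of This Study is that the intervention group will have better safety knowledge and behaviour "than children in the control group (ie, those who receive electronic and printed safety information) at 1- and 3-month follow-ups". Hypothesis 2 uses the same two time points.

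Baseline is brought into a model explicitly in one place only, a separate analysis within the intervention arm: "The association between total game points and pre–post changes in outcomes will also be analyzed using the linear mixed models". The group comparison has no corresponding statement.

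On school, the Participants section says: "Primary schools will be a blocking factor in randomization". Children are randomised 1:1 within each of four schools.

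**The concern.** The data have three levels: visits within children within schools. The article states the random part of the model and places it at school. The level at which measurements repeat, the child, is not mentioned, and nothing says whether the visits share one model.

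Two analysts could follow this text and do different things. One could put several visits per child into the model as described. The only correlation it then allows for is that between children of the same school, so repeat scores from one child are taken as new information. Carried-forward values make this worse, because an exact copy of an earlier score would count as an independent observation. A single group coefficient would also average over the visits instead of giving the effect at 1 month and at 3 months, and if baseline is included the average takes in a visit at which no effect can exist.

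The other analyst could fit the model once per follow-up. That is sound, but the text does not then say that the baseline score is used.

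At stake are the error rate of the main test, the quantity it estimates, and precision that could be had at almost no cost.

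**Working it through.** **Inputs from the article.** Standardised effect 0.181 (0.7 × 0.258 = 0.1806); 504 children per group; 80% power; 5% significance level; three assessments per child; randomisation within school.

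**Assumptions.** Two-sided test; SD 1 at every visit; equal correlation ρ between any two visits of a child, taken as 0.3, 0.5 and 0.7. The article gives no correlation.

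**1. The article's own figure.** For one comparison of two means, n per group = 2(1.96 + 0.842)² / 0.181², which rounds up to 480, or 960 in total. The stated 1008 is somewhat larger. With 504 per group the SE is √(2/504) = 0.063, and power is Φ(0.181/0.063 − 1.96) = 81.9%. The stated 80% is therefore met. This calculation uses one observation per child.

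**2. Visits stacked in the model as written.** With k visits per child:

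- SE reported by the model: √[2/(504k)]
- Actual SE: √[(2/504)(1 + (k − 1)ρ)/k]
- Type I error: 2[1 − Φ(1.96/√(1 + (k − 1)ρ))]

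| Waves stacked | ρ | Reported SE | Actual SE | Type I error |
|---|---|---|---|---|
| Three (k = 3) | 0.3 | 0.036 | 0.046 | 12.1% |
| Three (k = 3) | 0.5 | 0.036 | 0.051 | 16.6% |
| Three (k = 3) | 0.7 | 0.036 | 0.056 | 20.6% |
| Two follow-ups (k = 2) | 0.3 | 0.045 | 0.051 | 8.6% |
| Two follow-ups (k = 2) | 0.5 | 0.045 | 0.055 | 11.0% |
| Two follow-ups (k = 2) | 0.7 | 0.045 | 0.058 | 13.3% |

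**3. What the group coefficient estimates.** With true effects 0 at baseline and 0.181 at both follow-ups, stacking three waves gives (0 + 0.181 + 0.181)/3 = 0.121, two thirds of the effect. Stacking only the follow-ups gives (0.181 + 0.181)/2 = 0.181, so nothing is lost when the effect is equal at both.

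**4. Simulation check.** With 1008 children, four schools and 3000 runs per setting, stacking three waves gave type I errors of 11.8% / 16.1% / 19.7% and mean estimates of 0.121 / 0.119 / 0.118. School was fitted as fixed indicators, which is equivalent for this within-school balanced contrast.

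**5. One model per follow-up.** The formula gives a coefficient of 0.181, SE 0.063, type I error 5% and power 81.9%. The same simulation gave rejection rates of 4.7% / 5.1% / 4.7% under no effect, and power of 80.6% / 82.0% / 80.4%.

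**6. Adding the baseline score to the per-visit model.** Here ρ is the baseline to follow-up correlation and the SE becomes √[(2/504)(1 − ρ²)]:

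| ρ | SE | Power at 0.181 |
|---|---|---|
| no baseline score | 0.063 | 81.9% |
| 0.3 | 0.060 | 85.4% |
| 0.5 | 0.055 | 91.3% |
| 0.7 | 0.045 | 98.0% |

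**The case against.** The strongest reply is that the article never says visits are stacked. Its hypotheses are group differences at each follow-up, its sample size is a single two-group comparison, and a group term with a school intercept and covariates is just what a model with one row per child would contain. The school intercept alone accounts for the word mixed. On that reading the test is valid and nothing is diluted. This stands. A reader might infer that the plan has an inflated error rate and a diluted effect; the documents do not support that as an unconditional statement. Dilution needs a further step, that baseline is one of the stacked waves.

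A second reply is that a condensed article may leave time terms and covariance structure to a fuller document. This stands in part: that document may settle the matter, and an open covariate list does not exclude baseline or visit. But the article did choose to state the random structure and the group term, and what it states leaves room for two analyses with different estimates and error rates.

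A reader might also infer two further things that are not supported. One is that the model holds nothing beyond group and school; the covariates show otherwise. The other is that a random intercept from only four schools harms the test. Children are randomised within school, so group is nearly unrelated to school. A simulation of four schools of 252 children, 1000 runs per setting, gave the same rejection rate for random and fixed school at each school intraclass correlation tried (0, 0.02, 0.05, 0.10), with standard errors agreeing to 0.0001.

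**Conclusion.** The point holds in conditional form. The article specifies the effectiveness model without saying how three assessments per child enter it, and on either reading the stated terms can be improved.

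- **Stacked:** the standard error is too small by a factor of √(1 + (k − 1)ρ), that is 1.26 to 1.55 for three waves and 1.14 to 1.30 for two, over ρ from 0.3 to 0.7. One group coefficient does not give separate effects at 1 and 3 months. The loss of one third of the effect applies only if baseline is included, given equal effects at both follow-ups.
- **Per visit:** inference is sound, and the shortfall is precision. At the same assumed correlations, naming the baseline score would move power from about 82% to about 85%, 91% or 98%.

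All sizes rest on the assumed correlations and equal variances. This should be corrected before analysis. It is not evidence that the trial will be analysed wrongly.

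**What to change.** State one of two models for continuous outcomes.

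1. **Joint model.** Regress the 1- and 3-month scores on group, visit, group-by-visit, baseline score, school and the listed covariates, with a child random intercept or a within-child covariance. Report the group contrast separately at 1 and at 3 months.
2. **Separate models.** Fit one model per follow-up with group, baseline score, school and the listed covariates, and say that each visit is analysed on its own.

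In either case baseline enters as a covariate and not as an outcome row. School may stay a random intercept; three fixed indicators are an optional alternative.

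The cost is about two sentences in Data Analysis. Recruitment, data collection and sample size do not change, because the baseline score is already collected.

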### Sample Size Calculation

A previous intervention study reported a small-to-medium effect on road crossing behaviors (Cohen *d*=0.258) [23]. Assuming a conservative effect of 0.181 (70% of the previous study), 1008 participants (504 in each group) should be recruited to detect this effect size with 80% statistical power at 5% significance level.

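### The planned model has a random intercept for school only; leaving out the 48 classes keeps the test valid but gives up a small amount of precision in the linear models

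*Protocol article*

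**What the plan says.** All of this comes from the protocol article.

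- **Data Analysis.** The only grouping term is school: "School will be controlled as random intercepts". Fixed terms are the group allocation and "covariates, such as child’s age and sex and family socioeconomic status, will be adjusted as fixed independent variables". The list of covariates is open, but class is not mentioned as a fixed or a random term.
- **Participants.** "Among them, we will recruit 4 schools". The sample is built as "4 schools × 3 forms × 4 classes × 30 students × 70% = 1008 participants". Allocation is by child: "Participating students within each school will be randomized with a 1:1 allocation ratio into the intervention or control group". The design block is school: "Primary schools will be a blocking factor in randomization".
- **Sample Size Calculation.** The target is 504 children per group: "Assuming a conservative effect of 0.181 (70% of the previous study") and "to detect this effect size with 80% statistical power at 5% significance level".

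**The concern.** The random effect is given to the factor with four levels, which is a known design block. Nothing is given to the factor with 48 levels that the recruitment arithmetic rests on. Children in one class may resemble each other on safety knowledge and behaviour. If they do, the part of the outcome variance that class explains stays in the residual, and the interval for the treatment effect is wider than the same data allow. What is at stake is efficiency on the primary safety scores. Bias and type I error are not at stake.

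**Working it through.** **Inputs from the article.** 4 schools; 3 forms × 4 classes per school, so 4 × 3 × 4 = 48 classes; 30 × 0.70 = 21 participants per class; 48 × 21 = 1008 in total; 504 per arm; 1:1 within school; standardised effect 0.181; 5% significance, taken as two-sided because the sidedness is not stated.

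**Input assumed.** The class ICC, written r, is the share of within-school variance that lies between classes. The article gives no value, so 0.02, 0.05, 0.10 and 0.15 are used.

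**1. The plan's own figure.** With residual SD 1, the variance of the treatment effect is 2/504 = 1/252 and SE = 0.0630. Then 0.181/0.0630 = 2.873, and power = Φ(2.873 − 1.960) = 81.9%. The stated 80% is reproduced, with a little in hand.

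**2. School as fixed or random.** With 1:1 allocation inside each school, group is orthogonal to school. In 60 REML fits to simulated trials (school ICC 0.02, class ICC 0.05), the two versions gave treatment estimates that agreed to about 1e-15, and a mean SE of 0.0620 each. The school variance itself is poorly estimated from four units. The chance that it is estimated at zero is P(F(3, 1004) < 1/(1 + 252·s/(1 − s))) for school ICC s, which is 27.6%, 16.2% and 7.9% at s = 0.005, 0.01 and 0.02. Because of the orthogonality, this does not change the treatment comparison.

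**3. Validity without class.** In 3000 simulated null trials per setting (class ICC 0 to 0.10), the model without class rejected in 4.9% to 5.5%. That is nominal within simulation error.

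**4. Gain from a class random intercept.** Each school randomises 126 of its 252 children across 12 classes of 21. On average 11/251 = 0.0438 of the treatment contrast then lies between classes and 240/251 = 0.9562 lies within them. With known variance components, the variance relative to 1/252 is

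v = 1 / [0.9562/(1 − r) + 0.0438/(1 + 20r)]

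and power = Φ(2.873/√v − 1.960).

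| r | v | Variance cut | SE cut | Power |
|---|---|---|---|---|
| 0 | 1.000 | 0% | 0% | 81.9% |
| 0.02 | 0.993 | 0.7% | 0.4% | 82.2% |
| 0.05 | 0.972 | 2.8% | 1.4% | 83.0% |
| 0.10 | 0.928 | 7.2% | 3.6% | 84.7% |
| 0.15 | 0.880 | 12.0% | 6.2% | 86.5% |

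Example at r = 0.10: 0.9562/0.90 + 0.0438/3 = 1.0624 + 0.0146 = 1.0770, and 1/1.0770 = 0.928.

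The comparison above is with the planning variance 1/252. The sampling variance of the school-only estimator is slightly lower, at 0.9562(1 − r) + 0.0438(1 + 20r) of that. Measured against it, the cuts are 0.5%, 2.4%, 6.4% and 10.9%.

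**5. Cross-check by model fit.** In the same 60 REML fits, adding a class random intercept to fixed school effects lowered the mean SE from 0.0620 to 0.0611. That is 1.3%, against 1.4% in the table at r = 0.05.

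**6. Class as fixed effects instead.** This is not free. The SE rises about 2% at r = 0, breaks even near 0.05 and falls about 3% at 0.10.

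**The case against.** The strongest case against raising this is that nothing in the plan is wrong. The test is valid, planned power is already near 82%, and the gain rests on an ICC that the article does not give. Age largely tracks grade in Grades 4-6. Age and family socioeconomic status are already in the model and will absorb some between-class variance, and a baseline score would absorb more if it is used. An article also condenses its model, and a fuller plan may specify class. All of this stands as a limit on size, and it is why the point is minor. It does not remove the point, because the article does state its random-effects structure, and that structure passes over the classes.

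A reader might infer more than the documents support:

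- **That four schools are too few, so precision is lost or the block goes unadjusted.** The school variance is indeed imprecise and may be estimated at zero. With arms balanced within school, the treatment estimate and its SE are the same either way, so the loss comes only from class.
- **That ignoring class inflates type I error, as in a cluster-randomised trial.** Here the child is the unit of randomisation.
- **That classes share questionnaire sessions.** The article says only that children complete the items themselves, and the one group session it describes is a game briefing at each school.
- **That the change is free in every model.** In a logistic model, a class intercept turns a marginal odds ratio into a class-specific one. In a simulation at ICC 0.10 with class effects known, the log-odds estimate moved from 0.33 to 0.35 and its SE rose from 0.127 to 0.132.

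**Conclusion.** The point holds as a small efficiency gain forgone in the linear models. For class ICC 0.02 to 0.10, the variance of the treatment effect could be about 0.7% to 7% lower, and power at 0.181 would go from about 82% to between 82% and 85%. At 0.02 or below the gain is negligible. The ICC 0.15 row is shown only for range, since the article gives nothing to support it. The figures assume equal classes of 21, exact 1:1 allocation within school, known variance components and no covariates. They are therefore probably on the high side once age and socioeconomic status enter. The validity of the primary comparison is not in question.

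**What to change.** In Data Analysis, for the linear models of the continuous scores, state that the four schools enter as fixed effects because they are the randomisation blocks, and that class enters as a random intercept with 48 planned levels. State that each child's class is recorded at recruitment, since the article does not say that it is. Do not enter class as fixed effects, which costs precision when the ICC is low.

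The cost is three degrees of freedom for school, one extra variance component and one data field. Sample size and conduct are otherwise unchanged. Making school fixed is a matter of matching the model to the design and should not be presented as a gain in precision.

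For the logistic and Poisson models, decide separately whether the target is a marginal or a class-specific effect, and claim no narrower interval from a class intercept there.

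### The effectiveness model names its terms but not the baseline score of the outcome; saying how baseline enters would gain precision and limit the effect of chance imbalance

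*Protocol article*

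**What the plan says.** The Data Analysis section of the protocol article sets out linear mixed models for effectiveness. On the treatment term it says: "Group allocation will be included as dummy independent variable". School enters as random intercepts. On adjustment it introduces its covariates as examples, the child's "age and sex and family socioeconomic status, will be adjusted as fixed independent variables". The baseline score of the outcome does not appear among these terms, and neither does a time term, a group-by-time term or a child-level random effect. Pre-post change is mentioned only for the game-points analysis, which is confined to the intervention arm.

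The baseline scores will exist. For the child-reported safety items, the primary outcomes section says: "These items will be self-completed by the children at baseline and 1- and 3-month follow-ups". The Methods paragraph of the Abstract gives the same three occasions for the PedsQL and SDQ. The exception is the parent rating listed under the primary outcomes, which is itself a rating of change and is taken only at follow-up.

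The same Data Analysis section carries a dropout's previous assessment forward. For a child lost before month 1, that is the baseline value.

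**The concern.** The baseline value of a questionnaire score is usually the best single predictor of the same score at follow-up. Here it is collected for almost every outcome, yet the covariates chosen as examples are ones likely to be weaker. The target effect is small (d = 0.181), so the residual variance matters.

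Two things are at stake if the model is run with only the named terms. The standard error is larger than it need be. And a chance difference between the arms at baseline is partly carried into the estimated effect, more so for children whose baseline is carried forward. Leaving the main adjustment variable undeclared also means that the choice to adjust could be made after the data are seen.

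**Working it through.** **Inputs from the protocol article.** Sample Size Calculation: "Assuming a conservative effect of 0.181 (70% of the previous study), 1008 participants (504 in each group) should be recruited", "with 80% statistical power at 5% significance level". Participants: "Participating students within each school will be randomized with a 1:1 allocation ratio into the intervention or control group". Sidedness is not stated; two-sided is assumed. **Input not in the article:** the baseline to follow-up correlation r. It is assumed at 0.3, 0.5 and 0.7.

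**Step 1: the plan's own figure.** In SD units the standard error of the group difference is √(2/504) = 0.063. Power = Φ(0.181/0.063 − 1.96) = Φ(0.913), about 81.9%. The stated 80% holds without baseline adjustment. Exactly 80% would need 480 per arm, 960 in total.

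**Step 2: add the baseline covariate.** Residual variance is multiplied by (1 − r²), so SE = 0.063 × √(1 − r²) and power = Φ(0.181/SE − 1.96).

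| r (assumed) | Variance reduction | SE (SD units) | Power, 504 per arm | Total N for 80% power | Detectable d at 80% power |
|---|---|---|---|---|---|
| 0 | 0% | 0.063 | 81.9% | 960 | 0.176 |
| 0.3 | 9% | 0.060 | 85.4% | 874 | 0.168 |
| 0.5 | 25% | 0.055 | 91.3% | 720 | 0.153 |
| 0.7 | 51% | 0.045 | 98.0% | 490 | 0.126 |

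These are upper figures. The r in the formula should be the partial correlation given school, age, sex and socioeconomic status, since those terms may already account for part of what baseline explains. The calculation is for a continuous score.

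**Step 3: chance imbalance.** A baseline difference between the arms also has standard error 0.063 SD, so its 95% range is about ±1.96 × 0.063 = ±0.123 SD. For children with observed follow-up, about r times that difference reaches an estimate that is not adjusted for baseline:

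- r = 0.3: 0.3 × 0.123 = 0.037 SD, or 20% of 0.181
- r = 0.5: 0.5 × 0.123 = 0.062 SD, or 34% of 0.181
- r = 0.7: 0.7 × 0.123 = 0.086 SD, or 48% of 0.181

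For a child whose baseline is carried forward, the follow-up value is the baseline value, so the transfer is one for one. The article gives no dropout rate, so the combined size is not computed.

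**Step 4: could baseline enter as a response?** With three occasions it could in principle, but the named terms do not provide for it. Suppose baseline were one of three equally weighted responses under a single group term, with the same effect δ at both follow-ups. The coefficient would then average to (0 + δ + δ)/3 = two thirds of δ, because no effect can exist before the intervention. That reading therefore needs extra terms that the article does not state.

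**The case against.** The strongest objection is that the covariate list is illustrative. It is introduced as a set of examples, so a reader might infer that the model excludes baseline, but the article does not say so. It is a condensed account, and a fuller protocol or analysis plan that is not shown may complete the list. This stands: baseline is unnamed, not excluded. The point survives because the article goes into detail on the model's terms and still leaves out the covariate likely to matter most.

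Three further inferences are tempting, and the documents do not support them:

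- **That the result would be biased.** Children are randomized individually within schools, so leaving out baseline does not bias the comparison in expectation. The issue is precision and the consequence of chance imbalance in the one trial that is run.
- **That the trial would be underpowered.** The stated power is met without baseline adjustment.
- **That an imbalance passes in full into the estimate.** Only about r times it does, except for values carried forward from baseline.

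It is also fair to say that the gains rest on an assumed r, and that the starting point of 82% ignores whatever the named covariates already explain. Both are reasons to treat the power figures as upper limits.

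**Conclusion.** The point holds as one of incomplete specification with a real cost in efficiency. As written, the effectiveness model does not say how the baseline score enters, and the terms it names give baseline no route in. If it is run that way, the analysis is valid in expectation and reaches about 82% power, but it forgoes precision from data already collected and leaves chance imbalance uncorrected. With r assumed at 0.3, 0.5 or 0.7, power at d = 0.181 would rise to at most about 85%, 91% or 98%. An imbalance at its 95% limit would move the estimate by 20%, 34% or 48% of the target effect, before allowing for carried-forward baselines. These figures assume two-sided 5% testing, 504 per arm and a continuous outcome. The change is well worth making, but its absence is not a fatal flaw.

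**What to change.** Add one sentence to the Data Analysis section: for every outcome measured at baseline, the baseline value of that outcome is a fixed covariate in the effectiveness model. The alternative is to state that a repeated-measures model is used, with baseline as a response and its mean constrained equal across arms, and to name the time, group-by-time and child-level terms. State that this does not apply to the parent change rating, which has no baseline value. Nothing here argues for adding further covariates.

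The cost is one sentence and no new data. The article's Results section places recruitment in the future, so the sentence can be fixed before any outcome is seen.
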